**Figure 1. f1:**
[figure not shown]
Data flows to enable safe, secure transfer of patient identifiable data and linkage.

### Sample size

Assuming that around 80% of eligible staff and residents will participate, then on average approximately 38 residents and 49 staff will be tested per home across the 105 homes. Based on a conservatively estimated intra-cluster correlation of 0.36 (twice that reported for seasonal influenza
^13^) leads to effective sample sizes of around 279 residents and 285 staff, after accounting for the loss of precision due to clustering. Assuming an antibody prevalence of around 30% for both groups the precision of the estimate (based on 95% confidence interval width) will be ±5.4% for residents and for staff separately.

Importantly, as we anticipate that at least 1000 residents will have been infected at 3 months (using a conservative estimate of 20% infection prevalence), we should have sufficient precision and power to detect changes in antibody prevalence over time. For example, assuming 80% of infected residents agree to repeated antibody testing and 70% of these have an antibody response at 3 months (560 residents) then we can estimate the proportion of these retaining a response at 6 months within 4.2% assuming a retention rate of 50%. This assumes that antibody response is broadly unaffected by care home level factors.

### Outcomes

***Primary outcome***. The proportion of staff and residents who have previously been infected with SARS-CoV-2 based on presence of antibodies in serum at baseline, 6 weeks and 3 months.

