### Data linkage

We will undertake quarterly data linkage to Hospital Episodes Statistics, Mortality data and virological test results from March 1
^st^ 2020 onwards for all care home residents and staff. The legal basis for accessing identifiable data from all staff and residents without consent is provided through Covid-19: Notice under Regulation 3(4) of the Health Service Control of Patient Information Regulations 2002 (COPI)
^10^. Data linkage will continue for a period of up to 2 years as we anticipate that there will be additional waves of the pandemic in subsequent years.

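### The primary outcome labels antibody presence as previous infection; on the plan's own illustrative 70% response, the residents' 3-month figure could understate past infection by up to about 30% relative

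*Protocol article*

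**What the plan says.** Under Outcomes, the primary outcome is the share of staff and residents "who have previously been infected with SARS-CoV-2 based on presence of antibodies in serum at baseline, 6 weeks and 3 months". The summary of the analysis plan in the article reports it as sample proportions and models its risk factors by logistic regression with a random effect for care home. It mentions no adjustment for infected people without antibody.

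Under Sample size, the precision calculation starts from "Assuming an antibody prevalence of around 30% for both groups" and concludes that the precision "will be ±5.4% for residents and for staff separately". A second calculation, on durability of the response in residents, expects that "at least 1000 residents will have been infected at 3 months (using a conservative estimate of 20% infection prevalence", and goes on, as an example, "assuming 80% of infected residents agree to repeated antibody testing and 70% of these have an antibody response at 3 months (560 residents".

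Other evidence of infection is gathered. The Study schedule has a first PCR swab and two further rounds for all participants. The Data linkage section says: "We will undertake quarterly data linkage to Hospital Episodes Statistics, Mortality data and virological test results", reaching back to 1 March 2020 and covering all staff and residents. None of this enters the primary outcome. Under Secondary outcomes, the proportion with a new antibody response at 3 months is listed without saying whether people with earlier evidence of infection are set aside.

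**The concern.** Previous infection and present antibody are different quantities. Once a person has been infected, that fact cannot reverse; an antibody result can be negative because no response was made or because it was lost. The plan recognises this, since duration of the response is a secondary outcome and loss of response has its own Cox model. The primary outcome nevertheless treats the two as the same.

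Three things are at stake:

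- The Abstract and Introduction give the lack of reliable burden estimates as a reason for the study. A headline proportion that misses antibody-negative infections would be low, and a larger sample would not cure that.
- Differences between rounds would combine new infection with any loss of antibody.
- The risk-factor model would combine factors for becoming infected with factors for not making, or not keeping, antibody.

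**Working it through.** **Inputs** (Sample size section unless noted): 5,000 residents and 6,500 staff (Participants), 80% participation, 38 residents and 49 staff per home, intra-cluster correlation 0.36, antibody prevalence 30%; then 20% of residents infected at 3 months, 80% of these retested, 70% of those with antibody, 50% retention at 6 months. Specificity is not given; 98% to 100% is assumed.

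**Step 1: reproduce the plan's figures.**

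- Residents: 5,000 × 0.80 = 4,000; design effect 1 + 37 × 0.36 = 14.32; effective size 4,000 / 14.32 = 279. Half-width 1.96 × √(0.30 × 0.70 / 279) = 5.4 points.
- Staff: 6,500 × 0.80 = 5,200; design effect 1 + 48 × 0.36 = 18.28; effective size 5,200 / 18.28 = 284.5. Half-width 5.3 points.
- Durability example: 5,000 × 0.20 × 0.80 × 0.70 = 560. Half-width at 50%: 4.1 points by the normal approximation, 4.2 by the exact method.

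All agree with the stated 279, 285, ±5.4%, 560 and 4.2% to rounding. The arithmetic of the plan is not in question.

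**Step 2: apply the 70% to the primary outcome.** With infected proportion p, share of infected people with antibody Se, and specificity Sp:

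reading = Se × p + (1 − Sp) × (1 − p)

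With p = 0.20 and Se = 0.70:

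| Specificity (assumed) | Reading | Gap, points | Relative shortfall |
|---|---|---|---|
| 100% | 14.0% | 6.0 | 30% |
| 99.5% | 14.4% | 5.6 | 28% |
| 99% | 14.8% | 5.2 | 26% |
| 98% | 15.6% | 4.4 | 22% |

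For example, at 99%: 0.70 × 0.20 + 0.01 × 0.80 = 0.148.

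**Step 3: compare with the planned precision.** At perfect specificity the 6.0-point gap exceeds the stated ±5.4%. That half-width was computed at 30% prevalence; at a reading of 14% it is 1.96 × √(0.14 × 0.86 / 279) = 4.1 points. At 99% and 98% specificity the gap (5.2 and 4.4) is below 5.4, so the statement that bias exceeds the stated precision needs near-perfect specificity.

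**Step 4: read the other planning value backwards.** If 30% are antibody-positive, Se = 0.70 and Sp = 1, then 0.30 / 0.70 = 42.9% have been infected, a gap of 12.9 points and again 30% in relative terms.

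**Step 5: allow for scoring over rounds.** If a positive at any round so far counted, the relevant Se would be the share ever positive. At an assumed 90%, 20% infected would read as 18%, a 10% relative shortfall.

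**The case against.** The strongest reply is that the 70% is not an assay sensitivity. It is offered as an example, for residents who agree to repeat testing, at 3 months, to supply a denominator for the 6-month retention estimate. That stands. A reader might infer that the whole primary outcome is about 30% too low; the documents do not support this, because they give no such value for staff, for baseline or for 6 weeks.

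A reader might also take the 50% retention as proof that the measure falls between baseline and 3 months. It is not: that figure refers to 6 months, beyond the last primary time point, and no loss rate is given inside the window.

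A third inference is that residents who died before baseline should be added. They could not give serum. Counting them changes the target population, mortality has its own secondary outcome, and the death and resident counts in the Introduction are national rather than a roster of these homes.

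It can also be said that the definition openly states that it rests on serology, that new infection and antibody loss have separate analyses, and that the separate analysis plan may specify scoring over rounds or a correction for assay error. The first two are true but leave the headline quantity labelled as infection. The third could reduce the shortfall, but the outcome wording is fixed in the article, and infected people who never make antibody would still be missed by any-round scoring.

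Finally, replacing the primary outcome with an antibody-or-PCR composite has its own bias. The Introduction says testing had been limited, so linked results depend on who was tested. Serology applies one assay to everyone sampled and compares more readily with population seroprevalence, a stated secondary aim. This stands, and is why outright replacement is not recommended.

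**Conclusion.** The point holds in a limited form. The outcome names previous infection but measures antibody presence, and the plan's own example implies that the two differ materially. For residents at 3 months, with the illustrative 70% response and near-perfect specificity, past infection would be understated by up to about 30% relative: 20% infected would read as 14%. The shortfall is 22% to 28% at assumed specificities of 98% to 99.5%, and smaller if earlier positives count. For staff, baseline and 6 weeks the direction of the concern is the same wherever some infected people lack antibody and false positives are few, but the documents give no basis for a size.

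**What to change.** - Name the antibody proportion at baseline, 6 weeks and 3 months as seroprevalence.
- Beside it, for staff and residents separately, report cumulative evidence of infection to that round: antibody-positive at this or any earlier round, or PCR-positive on a study swab or on a linked result since 1 March 2020.
- Define the new antibody response among people with no earlier antibody or PCR evidence of infection, and state the date against which earlier is judged.
- Run the risk-factor model on both outcomes, and discuss differences between them.

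The cost is wording in the outcome section and analysis plan, plus one further set of proportions and models. No new samples or linkages are needed. The downside should be stated: linked PCR coverage was limited and uneven early in the pandemic, so the cumulative figure is a lower bound (false positives aside), and its risk-factor results may partly reflect access to testing.

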***Secondary outcomes***

The incidence and prevalence of acute infection and asymptomatic infection, at each round of swab testingThe proportion of residents and staff with a new antibody response to SARS-CoV-2 at 3 monthsThe proportion of residents with an antibody response to SARS-CoV-2 at 6 and 12 months, to investigate the duration of antibody response in this populationThe distribution of quantitative IgG and IgM responses to SARS-CoV-2 amongst staff and residents.Estimate the direct and indirect mortality in care home residents attributable to SARS-CoV-2Investigate transmission of SARS-CoV-2 between care homes, hospitals and the community by linking viral whole genome sequencing data from care home staff and residents to epidemiological information, and comparing sequences from the care home population to sequences that are circulating in local hospitals and the communityCompare disease incidence, seroprevalence and symptom profiles, in care home residents and the general population Evaluate the performance of PCR to detect infection using saliva versus nasopharyngeal swabsModel the risk of importation of infection to care homes following discharge of a resident from hospital by linking to data on hospital admissionsUse qualitative interviews to investigate the impact of the pandemic on ways of working in the care home, infection prevention control practices and behaviours, and to investigate how care home staff are interpreting and using Covid-19 test results.

### Data analysis and statistical analysis plan

A formal statistical analysis plan has been developed and can be accessed in the UCL data repository (extended data
^14^) and a summary is presented here. All data analyses will be performed using
Stata version 15.

The sample proportions of staff and residents will be presented as summary statistics for the primary outcomes, together with the proportion of care homes with any antibody detection. Univariate logistic regression modelling with random effects for care home will identify risk factors for the primary outcome which will subsequently be included in a multiple regression model.

The rates of antibody acquisition, hospital admission and mortality will be presented. Duration of antibody response will be described by a Kaplan-Meier curve. Appropriate regression modelling will be performed to establish risk factors and associated variables with each outcome and will be presented as hazard, odds or rate ratios. Associations with loss of antibody response and risk of death will be investigated using Cox regression models. Poisson regression modelling will be conducted to investigate risk factors for new antibody development during study period and for hospital admissions.

All analyses will be conducted separately for staff and residents. The detailed statistical analysis plan will include a methodology to handle missing testing data.

The plan for analysis of viral sequencing data has not yet been developed. The topic guide and analysis plan for the qualitative interviews is described in the CATCH-19 protocol available in the UCL data repository (extended data
^15^).

### Consent

Informed consent to participate will be collected in writing from all care home staff. Wherever possible, written informed consent will be sought directly from residents. Study information materials will be translated into other languages upon request. 

For residents who lack capacity, the care home will contact a friend or next of kin to act as personal consultee. If a personal consultee cannot be identified, a nominated consultee, such as the care home manager or a member of staff will be asked to complete a professional declaration form. This approach meets the four criteria for HRA approval as set out in sections 31–33 of the Mental Capacity Act 2005
^16^. This approach is also justified by the current lack of research in this population that can address important questions regarding impact and transmission of COVID-19.

### Data sharing

Research outputs will be published in open access journals and analytical code will be made available. A de-identified copy of the dataset will be made available for future research, however, decisions around the details shared will be made in partnership with FSHC. Fully anonymised transcripts from qualitative interviews will be archived in the
UCL Research Data Repository, where they will be made accessible to other researchers.

### Ethics

The study has been approved by the South Central - Hampshire B Research Ethics Committee (reference number 20/SC/0238).

### Dissemination

Rapid results from this study will be shared with national advisory committees and organisations who are leading the pandemic response. Results will also be shared with Four Seasons Health Care and participants. Planned publication in a high impact peer-reviewed journal within one year of study end date.

### Study status

At the time of protocol submission, all participating sites had been identified and recruitment had started.

This study has been registered with ISCRTN under registration number
14447421 on the 5
^th^ June 2020.

## Data availability

### Underlying data

No data are associated with this article.

### Extended data

UCL Data Repository: COVID-19 in care homes study (VIVALDI) - Symptom questionnaire.xlsx.
https://doi.org/10.5522/04/12764441.v1
^12^

- Symptom record V2 070720.xlsx (Symptom questionnaire administered to all study participants on the day of nasopharyngeal swab (SARS-CoV-2 PCR) that assesses for evidence of current infection)

UCL Data Repository: COVID-19 in care homes (VIVALDI) Statistical analysis plan.
https://doi.org/10.5522/04/12821633.v1
^14^

- VIVALDI analysis plan v1.2 final.pdf (Data analysis plan for VIVALDI-2 study performed by UCL researchers in 105 Four Seasons care homes across England)

UCL Data Repository: CATCH-19 topic guide.
https://doi.org/10.5522/04/12821663.v1
^15^

- CATCH-19_topic guide_V2_02.06.20.docx (Topic guide for CATCH-19 study qualitative interviews to be held with care home staff that are taking part in the VIVALDI study)

Data are available under the terms of the
Creative Commons Attribution 4.0 International license (CC-BY 4.0).
